**Fig. 2 Fig2:**
[figure not shown]
Schedule of enrolment, interventions, and assessments. Abbreviation: *SPIRIT* Standard Protocol Items: Recommendations for Interventional Trials

#### Outcome measures

##### Primary outcome measure

The primary endpoint is difference in evolution of AER from baseline to 3 months of intervention in absolute values as compared with placebo. AER will be measured in a 24-h urine sample at the clinical chemistry laboratory of the Erasmus Medical Center. The albumin level in urine will be measured by immunoturbidimetric assay (Roche Diagnostics GmbH, Mannheim, Germany).

##### Secondary outcome measures

The difference between intervention and placebo in change of AER expressed as percentage of baseline AER will be taken as a secondary outcome. Other secondary endpoints are the differences in the course of the established plasma markers of renal endothelial function (ADMA, sVCAM-1, sICAM-1, IL-6, and vWF) from baseline to 3 months. These markers will be measured by using enzyme-linked immunosorbent assays.

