##### Study procedure

At baseline, 6 weeks, and 3 months, 24-h urine will be collected for AER measurements. Information about demographic variables, lifestyle, adverse effects, compliance, and food intake will be collected by using standard questionnaires. The urine collection procedure starts in the morning and lasts 24 h; it stops at the same time point it started the day before. During collection, all of the produced urine is collected in a container that was handed out to the patient at the outpatient clinic. Within a couple of hours after the collection, urine is delivered in the outpatient clinic. AER is measured the same day as soon as possible after delivery. The patient is instructed to keep the container with urine in a dark and cool place at room temperature until delivery. At baseline and after 3 months, blood samples will be collected for determination of ADMA, sVCAM-1, sICAM-1, IL-6, and vWF and for measuring HbA_1c_ fasting glucose, lipids, creatinine, and estimated glomerular filtration rate (eGFR). Non-fasted venous blood is collected in EDTA tubes at a random moment of the day at the outpatient clinic. Plasma samples will be stored at −80 °C until analysis. Although patients are not required to fast before blood collection, we do keep a record of whether they fasted or not. In addition, body weight, blood pressure, and waist/hip circumference will be measured. In Fig. 2, we show a schedule of the study procedures. All participants receive usual care as provided by their diabetes team and must continue all of their prescribed medication, including adjustments when required. Since this may potentially affect our outcome measures, all used medications, dosage modifications, and other medical interventions during the trial will be recorded to adjust for this potentially confounding effect. We will ask the participants to keep their current lifestyle unchanged. There are no dietary restrictions during the study, except for the use of specific dietary supplement products containing at least 25 mg MOF. To control for dietary flavanols in regular food, we will use detailed dietary questionnaires to calculate the amounts.

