##### Statistical analysis

All analyses will be conducted in accordance with the intention-to-treat principle. We will use the mean (in case of normal distribution) and median values (in case of non-normal distribution) as measures of central tendency for numerical data and the standard deviation and interquartile range as measures of variability, respectively. Mixed modeling will be applied for longitudinal analyses of the data. Mixed modeling can efficiently handle data with missing and unbalanced time points. Three levels in the models will be postulated. The participating centers constitute the upper level, the patients the middle level, and their repeated measures the lower level. First, for each outcome variable, a model will be postulated, and the primary or secondary outcomes will be dependent variables. The models will include treatment group, time, and logarithm of time and treatment-time interactions as fixed effects. The deviance statistic [29] using restricted maximum likelihood [30] will be applied to determine whether the covariance structure should also include slope and intercept-slope interaction next to the intercept. No interim analysis will be performed. Analyses will be carried out by using SPSS version 21.0 (IBM, Armonk, NY, USA) (http://www-01.ibm.com/support/docview.wss?uid=swg21608060).

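### The percent-of-baseline AER outcome does not fit the one longitudinal model planned for every outcome; a baseline-adjusted log analysis answers the same question with somewhat more power

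*Protocol article*

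**What the plan says.** The protocol article defines two AER outcomes. The primary one (Primary outcome measure) is the "difference in evolution of AER from baseline to 3 months of intervention in absolute values as compared with placebo". The second, listed under Secondary outcome measures, is relative: it compares the arms on "change of AER expressed as percentage of baseline AER".

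AER is measured three times (Study procedure): "At baseline, 6 weeks, and 3 months, 24-h urine will be collected for AER measurements".

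The Statistical analysis section gives one model form for all outcomes: "First, for each outcome variable, a model will be postulated, and the primary or secondary outcomes will be dependent variables". The fixed part is set: "The models will include treatment group, time, and logarithm of time and treatment-time interactions as fixed effects". The random part holds at least a patient intercept, and the deviance is used "to determine whether the covariance structure should also include slope and intercept-slope interaction next to the intercept". The section names no exception for the percent outcome, no log transformation of AER and no baseline covariate.

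**The concern.** A percent change from baseline is a derived variable that equals 0 at baseline for every patient, whatever the treatment. A longitudinal model for three visits treats the baseline value as a random observation like the other two. Applied as written, the model must either take in a row without variance or lose that row, and with it the third time point that its time terms need.

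The sample size section expresses clinical relevance as a 20% change, so readers are likely to hold this outcome against that threshold. The mismatch is separate from the choice of scale for the primary endpoint: it would remain if only the primary analysis were changed.

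**Working it through.** **Inputs.** From Sample size calculation: mean AER 100, SD 40 (CV 0.40), correlation 0.70, a 20% fall on MOF, no change on placebo, 48 per arm. From Study procedure: three AER visits. Assumed: log-normal AER, complete data, no centre effect. CVs other than 0.40 are assumptions, used to show a range.

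The plan gives no figure for the percent outcome. Its 48 per arm belongs to the absolute-scale primary endpoint and serves here only as the size of the simulated trials.

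**1. Baseline kept.** In 4,000 simulated trials at CV 0.40, the variance of percent change at baseline, 6 weeks and 3 months is 0, 956 and 955, and the two later values correlate 0.49. A random intercept with one residual variance averages over the visits:
- mean variance: (0 + 956 + 955)/3 = 637
- mean covariance: (0 + 0 + 0.485 × 955)/3 = 155
- implied correlation: 155/637 = 0.24, against 0.49 in the data
- implied residual variance: 637 − 155 = 482

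So each visit's variance is wrong, and so is the correlation that would carry information from 6 weeks to a missing 3-month value. The variance implied for the change from baseline to 3 months is 2 × 482 = 964, close to the true 955. That is why the 3-month test survives in complete data: its simulated type I error is 4.3% at CV 0.40 and 4.9% at an assumed CV of 0.80.

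**2. Baseline dropped.** With visits at 6 and 13 weeks only, the columns for intercept, time and log time have rank 2 out of 3. The stated fixed effects cannot all be estimated. With three visits, using log(time + 1) because log 0 is undefined, the rank is 3.

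**3. Shift of the arm means.** For log-normal AER with log variance s² = ln(1 + CV²) and correlation ρ on the log scale, the mean ratio to baseline with no true change is exp[(1 − ρ)s²]. At CV 0.40, s² = ln(1.16) = 0.1484, so exp(0.30 × 0.1484) − 1 = +4.6%. With 0.70 read as the correlation of raw AER, the log covariance is ln(1 + 0.70 × 0.16) = 0.1062, and exp(0.1484 − 0.1062) − 1 = +4.3%. A true 20% fall then shows as 0.80 × 1.043 − 1 = −16.5%.

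**4. Shift of the contrast.** Both arms carry the same factor. The difference is 0 under no effect. Under a 20% fall it is −20 × 1.043 = −20.9 points at CV 0.40. At assumed CVs of 0.60 and 0.80 it is −21.7 and −22.7.

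**5. Power.** Six thousand trials per setting, 48 per arm, 3-month comparison, ρ = 0.70 on the log scale:

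| CV | t-test, percent change | t-test, log change | ANCOVA, log AER |
|---|---|---|---|
| 0.40 (stated) | 0.943 | 0.950 | 0.973 |
| 0.60 (assumed) | 0.670 | 0.708 | 0.774 |

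At CV 0.40 the step from percent to log gives 0.7 points and the baseline covariate 2.3. At CV 0.60 the two steps give 3.8 and 6.6 points. With the same random-intercept model (time saturated) on both scales, power is 95.5% for percent against 96.5% for log at CV 0.40, and 50% against 58% at an assumed CV of 0.80.

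**The case against.** The strongest case for leaving the plan alone is that little goes wrong with the quantity it defines. The outcome is a difference between arms, and the upward shift of a mean ratio cancels under no effect. At the stated SD it moves a 20% effect by about 1 point, type I error holds, and the scale alone costs about 1 point of power on an outcome for which the trial was not sized. All of this stands.

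A reader might go further and infer that the trial would report misleading percent changes: a rise on placebo that did not occur, and too small a fall on MOF. The article does not support that. It nowhere says that mean percent changes will be given per arm, and for non-normal data it foresees medians as the descriptive summary. In the log-normal model used here the medians are unshifted. A reader might also credit the whole power gain to the log scale; at the stated SD most of it comes from adjusting for baseline.

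Two further objections stand in part. The conflict between time terms and number of visits is not peculiar to this outcome, since the plasma markers are taken only at baseline and 3 months under the same model. It applies to the percent outcome all the same. And an analysis plan that is not shown may treat the derived variable in its own way. But the article itself fixes both the outcome and the model for every outcome, and those two statements do not fit together.

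**Conclusion.** The point holds as a mismatch between outcome and model. With baseline included, the planned covariance structure misdescribes a variable that has no variance at the first visit; with baseline excluded, the planned time terms cannot be estimated. The practical cost is moderate: power of about 0.94 against 0.97 at the stated SD and correlation, and about 0.67 against 0.77 at an assumed CV of 60%.

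There is no material bias in the between-arm contrast and no inflated type I error. The upward shift of about 4.5% concerns only arm-level means, should they be reported.

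These sizes rest on log-normal AER and complete data. Unbalanced missing data, centre effects and random slopes were not simulated, so the effect of the wrong correlation on incomplete data is argued here but not measured. This is a worthwhile improvement to a secondary outcome and does not threaten the trial's main conclusion.

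**What to change.** In Secondary outcome measures, define the relative AER outcome as the ratio of geometric means, MOF to placebo, at 3 months. In Statistical analysis, give it its own model: ln(AER) at 6 weeks and 3 months, with baseline ln(AER) as covariate, visit as a category, and treatment by visit. Alternatively, model all three visits with a common baseline mean for the two arms. Report exp(treatment difference at 3 months) − 1 as the percent difference, with its 95% CI. In the simulations the log analysis returns a ratio of 0.80 for a true 20% fall, without shift.

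The cost is about one sentence in each section, with no new data and no extra patients. The downside is that results are reported as geometric means, which some readers find less familiar than a mean percent change.

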##### Other study parameters

HbA_1c_, fasting glucose, lipids, eGFR, and plasma creatinine will be measured at the clinical chemistry laboratory of the Erasmus Medical Center by using routine lab techniques.

##### Data monitoring

All data will be filed and managed by using the trial management system OpenClinica (Waltham, MA, USA). Data will be entered into OpenClinica with a consecutive code number (no initials or birth date). Human material (blood samples) will also be encoded and kept at −80 °C until analysis. The subject identification code list, which links the code number to the participant, will be safeguarded by the secretary of the department of internal medicine in a “master file”. The key to the code is accessible by the investigators only. Study data can be accessed only by the investigator team, staff of the Health Care Inspection, and members of the Medical Ethical Committee, as stated in the informed consent form. The handling of personal data will comply with the Dutch Personal Data Protection Act (in Dutch: De Wet Bescherming Persoonsgegevens, WBP). All data, urine, and blood samples will be kept for a maximum of 15 years after the trial has finished.

An independent data monitoring committee (DMC) will be established in accordance with research integrity guidelines of the Erasmus Medical Center. The current trial has been identified as a trial with minimal risk for the participants and therefore the frequency of monitoring by the DMC will be only once a year. During this monitoring visit, the following items will be checked: the trial master file, inclusion speed, informed consent (sample of 10% of the participants), inclusion and exclusion criteria (sample of 1–10%), compliance with the protocol (sample of 1–10%), source document verification (sample of 1–10%), (serious) adverse events (sample of 1–10%), instructions of study procedures, certification of laboratories involved, and the labeling and storage of biological samples.

##### Public disclosure and publication policy

The results of this trial will be disclosed unreservedly. We registered the trial before its start in the Netherlands Trial Registry. Our intention is to publish the results as soon as possible after completion of the sample analyses and data evaluation in an appropriate peer-reviewed scientific journal.

##### Safety

In case of a suspected serious adverse event (SAE), the investigator will report the SAE to the sponsor without undue delay after obtaining knowledge of the event. Via the web portal ToetsingOnline, the sponsor will report the SAEs to the accredited METC (the medical research ethics committee, which approved the protocol) within 7 days of first knowledge for SAEs that result in death or are life-threatening followed by a period of a maximum of 8 days to complete the initial preliminary report. All other SAEs will be reported within a period of 15 days after the sponsor has first knowledge of the SAEs. Because of the low risk associated with the investigational product, no data and safety monitoring board or safety committee will be established.

##### Statistical analysis

All analyses will be conducted in accordance with the intention-to-treat principle. We will use the mean (in case of normal distribution) and median values (in case of non-normal distribution) as measures of central tendency for numerical data and the standard deviation and interquartile range as measures of variability, respectively. Mixed modeling will be applied for longitudinal analyses of the data. Mixed modeling can efficiently handle data with missing and unbalanced time points. Three levels in the models will be postulated. The participating centers constitute the upper level, the patients the middle level, and their repeated measures the lower level. First, for each outcome variable, a model will be postulated, and the primary or secondary outcomes will be dependent variables. The models will include treatment group, time, and logarithm of time and treatment-time interactions as fixed effects. The deviance statistic [29] using restricted maximum likelihood [30] will be applied to determine whether the covariance structure should also include slope and intercept-slope interaction next to the intercept. No interim analysis will be performed. Analyses will be carried out by using SPSS version 21.0 (IBM, Armonk, NY, USA) (http://www-01.ibm.com/support/docview.wss?uid=swg21608060).

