## Methods/design

### Study design

This study is a double-blind, randomized, controlled, multicenter trial. After giving written informed consent, eligible participants will be randomly assigned to placebo or intervention for 3 months. Outcome parameters will be measured at baseline, at 6 weeks, and at 3 months. In Fig. 1, we show the flow chart of this study. The SPIRIT (Standard Protocol Items: Recommendations for Interventional Trials) checklist for study protocols is provided as an Additional file 1.

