### Randomization and blinding

Patients will be randomly assigned to either intervention or control group at an allocation ratio of 1:1. All investigators, medical staff, statisticians, and participants are blinded to the intervention. The statistician generates the allocation sequence and delivers it to the nutritional company responsible for the preparation of the product and placebo. The nutritional company produces the research product and placebo using the same packages without labels of the company or product name. We do not mention the product or company’s name to the participants. The sachets are packaged in boxes containing the appropriate amount for a 3-month intervention of an individual subject. The boxes are labeled with a unique numerical code, derived from the generated allocation sequence. They will be given to the participants in consecutive order. To avoid bias, the consecutive order of the labeled boxes is strictly followed. Thus, the first recruited patient is handed box number 1, the second patient is handed box number 2, and so on, regardless of the center of recruitment. Furthermore, the nutritional company prepares two identical sealed boxes, each containing 114 numerical coded envelopes with the respective treatment allocation inside. One sealed box will be stored at a secured place where only the principal investigator has direct access; the other sealed box will be kept at a secured place at the office of the head of the department. Only in case of a medical urgency is the blinding code to be broken. The designated physician and the principal investigator are ultimately responsible for the final decision of breaking the code for a single subject. Otherwise, decoding will first take place after a blind review including preliminary statistical analyses of the primary outcome data by an independent statistician. In all cases, unblinding will take place in the presence of a witness.

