### Sample size calculation

Considering a clinically relevant effect of 20% change of albumin excretion rate (AER), which is half the effect of angiotensin-converting enzyme inhibitors (ACEis) on AER [24, 25], we estimated that the average AER of 100 decreased to 80 μg/min albumin (standard deviation 40) in the intervention group compared with no expected change in the placebo group. With a two-sided alpha set at 0.05 and power at 0.80 and a correlation of 0.70 between the three repeated measures, we calculated that at least 48 patients in each study group (i.e. 96 in total) would be required [26].

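### The stated mixed model gives each arm its own baseline AER mean, so the 3-month contrast has only change-score precision; a common baseline would cut its variance by 15% at the plan's correlation

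*Protocol article*

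**What the plan says.** The Statistical analysis section of the protocol article describes a mixed model with centre, patient and repeated measure as its levels, and lists the fixed effects: "The models will include treatment group, time, and logarithm of time and treatment-time interactions as fixed effects".

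Study design gives the visits: "Outcome parameters will be measured at baseline, at 6 weeks, and at 3 months". The sample size calculation counts the same three, assuming "a correlation of 0.70 between the three repeated measures". The primary outcome is the between-arm difference in the course of absolute AER from baseline to 3 months. Baseline is therefore part of the outcome vector.

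The article mentions neither a common baseline mean nor baseline AER as a covariate. The adjustments it describes, under Study procedure, concern changes in medication and medical care and dietary flavanols. Baseline AER otherwise appears only as the denominator of a secondary outcome, percentage change.

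**The concern.** When baseline is an outcome and treatment has a main effect, the model estimates a free between-arm difference at time zero. Randomisation makes the true difference there zero, because baseline precedes treatment. Estimating a quantity that is known to be zero costs precision in the contrast that matters, the 3-month difference in change.

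At stake is the width of the confidence interval for the primary endpoint and some of its power. How much is lost depends on the correlation between baseline and 3-month AER: the weaker it is, the larger the loss.

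**Working it through.** **Inputs, all from the protocol article.** Difference 20 μg/min ("the average AER of 100 decreased to 80", no change expected on placebo). SD 40, read here as the SD of one AER measurement. Correlation r = 0.70. "With a two-sided alpha set at 0.05 and power at 0.80". Sample size: "at least 48 patients in each study group (i.e. 96 in total) would be required". Allocation to "either intervention or control group at an allocation ratio of 1:1".

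**The plan's own figure.** With n per arm = 2(1.96 + 0.8416)² × 40² × f / 20² and variance factor f:

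- single follow-up value, f = 1: 63
- mean of three measures, f = (1 + 2r)/3 = 0.80: 51 (power 78.2% at 48)
- change from baseline, f = 2(1 − r) = 0.60: 38
- baseline-adjusted, f = 1 − r² = 0.51: 33

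None gives 48. The change-score figure with 20% dropout does (38/0.8 = 47.5, rounded up to 48), but the article states no dropout rate. The formula source it cites is not available here. The comparison below does not depend on how 48 was obtained.

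**What the stated model estimates.** An intercept, time and log time, each with a treatment term, give each arm three free means at three visits. With complete data the 3-month contrast is then exactly the difference in mean change, whether or not a random slope is added. A generalised least squares calculation (equal correlation 0.70, SD 40, 48 per arm, log(time + 1) assumed) confirms this. The SE is 6.325 with both interactions, and 6.318 to 6.325 with a linear interaction only. A common baseline mean gives 5.80 to 5.83.

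**Size at r = 0.70.** SE = 40 × √(2f/48) and power = Φ(20/SE − 1.96).

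| Model | f | SE (μg/min) | Power at 48 per arm |
|---|---|---|---|
| As stated | 0.60 | 6.32 | 88.5% |
| Common baseline or baseline covariate | 0.51 | 5.83 | 92.9% |

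The variance ratio is 0.51/0.60 = 0.85. Put differently, 48 per arm would do the work of 48/0.85 ≈ 56.

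**Other correlations.** The ratio (1 − r²)/[2(1 − r)] equals (1 + r)/2:

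- r = 0.50: 0.75, a 25% saving
- r = 0.70: 0.85, a 15% saving
- r = 0.90: 0.95, a 5% saving

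If the correlation decayed from 0.70 between adjacent visits to 0.49 between baseline and 3 months (an assumption, not in the article), the stated model would have SE 8.25 and power 67.9%. The common-baseline model would have SE 7.12 and power 80.2%.

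**Chance imbalance.** The baseline difference between arms has SE 40 × √(2/48) = 8.2 μg/min. Given an observed difference d, the change contrast is shifted by −(1 − r)d, or 0.30 × 8.2 ≈ 2.4 μg/min for a one-SE imbalance. This is the same loss seen from another side. The gap between the factors is 2(1 − r) − (1 − r²) = (1 − r)² = 0.09. In variance terms, 1600 × 0.09 × 2/48 = 6, which is the difference between 1600 × 0.60 × 2/48 = 40 and 1600 × 0.51 × 2/48 = 34.

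**The case against.** Treatment, time and their interaction form a standard and valid analysis that matches the stated endpoint. On the article's own inputs a change score at 48 per arm has about 88% power, above the planned 80%. All of this stands, and it makes the point one of efficiency.

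Three stronger readings are tempting, and the document supports none of them.

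- *The estimate is biased by baseline imbalance or regression to the mean.* Under randomisation the change contrast is unbiased, and regression to the mean acts on both arms equally in expectation. Only the conditional shift shown above remains, and it is already counted in the variance.
- *Baseline AER is ignored.* It serves as the reference for change, which at r = 0.70 already lowers the factor from 1 to 0.60. It is used, but not in the most efficient way.
- *The trial is underpowered because of this model.* That does not follow at r = 0.70; it would need a lower correlation than the plan assumes.

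The article is condensed, so a fuller protocol or analysis plan may list further covariates. However, the treatment main effect is stated, and so is baseline's place among the repeated measures. Moving baseline out of the outcome vector would conflict with the three repeated measures, and would leave two visits to support an intercept, time and log time.

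Deleting the main effect is not automatically safe either. The logarithm of time is undefined at zero and the article gives no time coding. If baseline were coded as 1, log time would vanish there but the linear treatment-by-time term would not, and the deletion would impose a wrong constraint. This objection stands and shapes the fix.

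**Conclusion.** The point holds as a free improvement. The stated model gives a valid, unbiased estimate with change-score precision. A common baseline mean, or baseline AER as covariate, would estimate the same treatment effect with 15% less variance at r = 0.70, and power at 48 per arm would be about 93% instead of 88%.

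The variance ratio depends only on the correlation between baseline and 3-month AER, assuming equal variances at the two visits and complete data. The power figures also rest on reading SD 40 as the SD of a single measurement, a reading on which the planned 48 per arm is not reproduced without an unstated allowance for dropout.

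**What to change.** Before unblinding, prespecify one of two models for AER:

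1. **Common baseline mean.** Keep all three measurements as outcomes, omit the treatment main effect, and code time so that every treatment-time term is zero at baseline. Categorical visit with treatment-by-visit terms at 6 weeks and 3 months does this. So does time with baseline at 0 and log(time + 1). State the coding.
2. **Baseline as covariate.** Model the 6-week and 3-month AER, with baseline AER as a covariate.

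The first keeps the mixed model's handling of incomplete follow-up and the endpoint as worded. The cost is a changed model term and a sentence on time coding, with no new data and no change to sample size. Under Trial status recruitment is still open at this protocol version, and Randomization and blinding places routine decoding after a blind review, so there is time to record the change.

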### Study population

Patients with T2D will be recruited from the diabetes outpatient clinic of the Erasmus Medical Center in Rotterdam and the community hospitals of Havenziekenhuis, IJsselland Ziekenhuis and Ikazia Ziekenhuis as well as GP-clinic Stichting Gezond op Zuid in Rotterdam. Patients who attend the diabetes outpatient clinics of the participating centers will be screened for eligibility through assessing their medical records by the study coordinator (MR). Then eligible patients are informed by their designated physician about the trial during a routine control appointment. If the patients are interested, the study coordinator provides them with a flyer and additional information at the outpatient clinic. Hereafter, patients will be given at least 2 weeks to decide whether they want to participate. Inclusion is complete after signing the informed consent form.

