### Inclusion criteria

T2D, as defined in the section aboveAge of 40–85 yearsMicroalbuminuria in the previous 6 months (as microalbuminuria can change during time, results should not be older than 6 months), defined as one of the following:30–300 mg albumin in a 24-h urine sampleor 3.5–35 mg albumin/mmol creatinine in females and 2.5–25 mg albumin/mmol creatinine in males in a urine portion.

This definition is derived from the Dutch national guidelines [23].

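### The stated AER model does not condition on pre-treatment albuminuria: adjusting for the baseline AER, and then for the qualifying urine result, would be a cheap gain in precision

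*Protocol article*

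**What the plan says.** Under Primary outcome measure, the protocol article states: "The primary endpoint is difference in evolution of AER from baseline to 3 months of intervention in absolute values as compared with placebo". Under Study procedure: "At baseline, 6 weeks, and 3 months, 24-h urine will be collected for AER measurements". The Statistical analysis section describes a three-level mixed model (centre, patient, repeated measure) and adds: "The models will include treatment group, time, and logarithm of time and treatment-time interactions as fixed effects".

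The Inclusion criteria require a microalbuminuria result no older than 6 months. It may be 30–300 mg of albumin in a 24-h sample, or a ratio of "3.5–35 mg albumin/mmol creatinine in females and 2.5–25 mg albumin/mmol creatinine in males in a urine portion". According to Study population, patients "will be screened for eligibility through assessing their medical records by the study coordinator", so this result predates consent and is separate from the baseline collection. Each randomised patient therefore has two pre-treatment albuminuria values. The stated fixed effects use neither as a covariate.

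The Sample size calculation assumes that "the average AER of 100 decreased to 80 μg/min albumin (standard deviation 40) in the intervention group", with no change on placebo and "a correlation of 0.70 between the three repeated measures", and arrives at 48 patients per group.

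**The concern.** A single 24-h AER measures a patient's usual level with a good deal of noise; the assumed correlation of 0.70 between visits says as much. When the baseline is only one of the repeated outcomes, and each group has its own baseline mean, the treatment-by-time contrast is a difference in change from baseline. The noise in the baseline then passes in full into the comparison. Conditioning on the baseline removes part of it, and a second pre-treatment value can remove a little more.

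Both values are fixed before randomisation, so pre-specified adjustment for them does not bias the comparison. What is at stake is the width of the confidence interval for the primary AER difference in a trial of 96 patients, not its validity.

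**Working it through.** **Inputs from the Sample size calculation.** Difference 20 μg/min, SD 40, two-sided alpha 0.05, power 0.80, correlation 0.70, 48 per group. Variances below are multiples f of the single-visit variance (40²), with equal correlation between visits. SE = 40·√(2f/48).

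**The plan's own figure.** N per group = 2·40²·f·(1.960 + 0.842)²/20². The nearest simple reading is the mean of three measures, f = (1 + 2·0.70)/3 = 0.80. This gives N = 50.2, rounded up to 51, and power 78.2% at 48 per group: close to the stated 80%, though not exactly 48. The points below do not depend on which formula was used.

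**Step 1: conditioning on the baseline AER.**
- Difference in change: f = 2(1 − 0.70) = 0.60, SE 6.32 μg/min, power 88.5% for 20 μg/min.
- Baseline as covariate: f = 1 − 0.70² = 0.51, SE 5.83, power 92.9%.
- Cut in variance: 1 − 0.51/0.60 = 15%.

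**Step 2: adding the qualifying value Q to the baseline-adjusted model.** Let q be the correlation of Q with both the baseline and the 3-month AER. The document does not give q, so it is an assumption. Then f = 1 − (0.49 + q² − 1.4q²)/(1 − q²). With 96 patients, each extra coefficient costs roughly 1/96 of the variance. Two coefficients at the 3-month visit (Q and test type) multiply f by about 1 + 2/96 = 1.021.

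| q (assumed) | f | cut against 0.51 | net of two coefficients |
|---|---|---|---|
| 0.7 | 0.4235 | 17.0% | about 15% |
| 0.6 | 0.4594 | 9.9% | about 8% |
| 0.5 | 0.4800 | 5.9% | about 4% |
| 0.4 | 0.4929 | 3.4% | about 1% |
| 0.3 | 0.5011 | 1.7% | none |

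If Q tracks the baseline better than month 3, the gain shrinks. Correlations of 0.6 and 0.5 give f = 0.50 (2.0% before the cost of coefficients); 0.6 and 0.42 give f = 0.51 (nothing). Simulation with AER in absolute values, as the endpoint is defined, gave about 0–9% net under assumed variability.

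**Step 3: adding Q to the current model.** The contrast is within patients, so a patient-level main effect cancels. Fitted to one simulated data set, the SE of the 3-month interaction was 6.454 with and without Q. Giving Q its own coefficient at each visit, without conditioning on the baseline, does not help either when q is the same at both visits: f stays at 0.60, and the simulated SE was 6.40 against 6.37. The gain in step 2 therefore needs step 1 first.

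**The case against.** The strongest reply is that nothing here is wrong. The stated model gives a valid comparison, and no stated figure relies on the qualifying value. The list of fixed effects may also be incomplete: Study procedure plans to record medication changes for adjustment and to control for dietary flavanols, and a full analysis plan may name further covariates. This stands, and it is why the point is an optional improvement. It does not remove the point, because the terms that are listed lead to the less precise contrast, and the adjustments mentioned elsewhere do not include pre-treatment albuminuria.

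A reader might infer that the qualifying result is worth 17% of the variance, as if the trial had 48 × 0.51/0.4235 ≈ 58 patients per group. The document does not support that. Its 0.70 applies to three trial AERs, all from 24-h urine within 3 months. The qualifying value comes from records, may be 6 months old, is restricted by the entry limits, and may be a spot ratio. The 17% is a ceiling before the cost of coefficients.

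A reader might also take the gain to be free. It is not: at an assumed correlation of 0.4 the extra coefficients use up more than half of it, and at 0.3 all of it.

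Finally, at the planned 20 μg/min and SD 40, the single 3-month contrast already has 88.5% power under the change analysis, so the plan's own assumptions show no shortfall that this must repair.

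**Conclusion.** The point holds as a minor, inexpensive gain in precision. The firmer part is conditioning on the baseline AER: 15% less variance for the 3-month contrast, resting on the plan's correlation of 0.70, equal variances and equal correlation between visits. The part due to the qualifying value is smaller and uncertain: about 0–8% net for assumed correlations of 0.3–0.6, and possibly nothing if that value predicts the baseline much better than month 3. Only a value as good as a trial AER would reach 15–17%. Reading the omission as an error in the analysis, or as a loss equivalent to a stated number of patients, goes beyond what the document shows.

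**What to change.** Before unblinding, pre-specify for AER a mixed model that conditions on the baseline AER, either as a covariate for the 6-week and 3-month values or through a baseline mean constrained to be equal in the two groups.

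In that model add log(qualifying value ÷ lower entry limit for that test and sex), where the limits are 30 mg per 24 h, 3.5 mg/mmol for females and 2.5 mg/mmol for males. Include an indicator for test type and a separate coefficient at each visit. All three entry ranges span exactly tenfold, so this puts every patient on a common 1–10 scale before the log; the indicator allows for the remaining difference between a 24-h amount and a spot ratio. Do not add the qualifying value as a main effect to the current model.

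The cost is two to four degrees of freedom, a changed form for the primary model, and transcription of the qualifying value and test type from the eligibility record. No extra visit, sample or patient is needed. If only one change is made, conditioning on the baseline AER is the one to keep.
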